## Adaptation

Although the adaptation of the NFP program closely adhered to its original guidelines and curriculum, several key differences were implemented in the German version. A significant change was made regarding the professional background of the family companions. While the U.S. NFP program employs family nurses (specially trained pediatric nurses), the ProKind study utilized state-certified and NFP-trained midwives as family companions. This change was based on the strong integration of midwives in Germany's primary healthcare system. In Germany, midwifery is a highly respected profession providing care and support to individuals during pregnancy, childbirth, and the postpartum period. The legal foundations are regulated through the Midwifery Act (HebG) and the Midwifery Training and Examination Regulation (HebAPrV), which define the requirements for professional practice, including a state-recognized three-year training program with theoretical and practical components, a state examination, regular continuing education, and comprehensive documentation duties. Additionally, midwives must document all treatments and maintain these records for at least ten years. Furthermore, German law guarantees every woman statutory midwifery care during pregnancy, delivery, and the first twelve weeks postpartum. This statutory assistance, however, focuses exclusively on health-related aspects, is limited in duration, and does not follow a structured curriculum. All family companions in the ProKind study were required to have extensive experience working with families experiencing adversities and to demonstrate a respectful and sensitive approach to the mothers. Consistent with the NFP model, only female family companions were employed to foster trust and rapport with the participants.

Additionally, the ProKind study evaluated two different delivery models for home visits. In the first model, visits were conducted exclusively by midwives, referred to here as the Continuous Model (CM), which closely aligns with the original NFP program. In the second model, referred to as the Tandem Model (TM), the intervention was carried out by a team consisting of a midwife and a state-certified social worker (equivalent to a bachelor's degree in social work). In this model, the midwife conducted visits during pregnancy, while the social worker took over approximately two months after the birth. The conceptual rationale for the TM was twofold: (a) In Germany, prenatal and perinatal care provided by midwives is generally covered by statutory health insurance, while early childhood social support for disadvantaged families is funded through social legislation. The TM sought to align with these financing structures, and (b) the TM aimed to leverage the distinct competencies of midwives and social workers. Midwives contributed medical expertise in areas such as childbirth, infant nutrition, and early child development, while social workers provided case management skills and experience in addressing child abuse and neglect within institutional frameworks.

However, current empirical evidence indicates that the quality of the relationship between practitioner and family is a key driver of effectiveness in preventive home-visiting programs (63, 64). A central strength of the original NFP model lies in the therapeutic relationship between the nurse and the first-time mother, which is deliberately fostered through continuity, trust, and long-term engagement (9, 65). Since the TM involves a handover from midwife to social worker shortly after birth, it may potentially entail the risk of interrupting this continuity of care at a particularly sensitive developmental stage. Such a transition could make it more difficult for families to establish and maintain a stable working alliance, which is regarded as a central mechanism of program effectiveness. Continuous support by a single professional, as implemented in the CM, may therefore be more conducive to sustaining trust and engagement. Taken together, these considerations suggest that the TM could potentially entail certain structural disadvantages compared to a faithful adaptation of the original NFP design that emphasizes relational continuity as a core element of its effectiveness.

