## The German adaption of NFP – the ProKind study

In Germany, the concept of early intervention (“Frühe Hilfen”) was introduced in the 1970s as part of healthcare and child welfare programs [Nationales Zentrum Frühe Hilfen (NZFH)]. Despite the development of numerous initiatives, there was a lack of comprehensive evaluation research (61). To address this gap, the Federal Ministry for Family Affairs, Senior Citizens, Women and Youth (BMFSFJ) launched the “Early Support and Social Early Warning Systems” program in 2006. These efforts led to increased attention and conceptual differentiation of early support measures in Germany, particularly regarding prevention and child protection. One such initiative is the ProKind study, a multicenter RCT adapting the NFP program for Germany (40). The intervention within the ProKind study was conducted between 2006 and 2012 in the German federal states of Bremen (a city-state in northern Germany known for its urban environment and relatively high levels of social disparities), Lower Saxony (a largely rural state with pockets of urbanization and a diverse socio-economic landscape), and Saxony (an eastern state characterized by its post-reunification socio-economic challenges and unique demographic structure).

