## Sample at baseline and randomizations procedure

At the time of baseline data collection (2008–2009), women in the 12th to a maximum of the 28th gestational week were recruited based on the following inclusion criteria: (a) an ongoing pregnancy (<28 weeks), (b) at least one financial risk factor [e.g., receipt of unemployment benefits (ALG II), debt], (c) at least one additional social or personal stress factor (e.g., being underage, lack of a school diploma, personal experiences of abuse or neglect) and (d) at least basic knowledge of the German language to enable communication with the German-speaking family companions (≙ A1–A2 language level). Participants were recruited through various intermediaries, including gynecologists, midwives, youth welfare offices, psychosocial counseling centers, and employment agencies. In total, *N* = 1.157 interested pregnant women registered to participate in the project. Of these, *n* = 263 did not meet the inclusion criteria, and *n* = 139 declined participation after receiving detailed information about the project. The final sample of *N* = 755 women was randomly assigned to an intervention group (IG, *n* = 394) or a control group (CG, *n* = 361) using Efron's Biased Coin Design (62), stratified by municipality (urban vs. rural), age (≤18 vs. >18 years), and maternal nationality (German vs. non-German). The women were, on average, 21 years old at the start of the project; approximately 88% were unmarried (about 28% were single parents), and about 12% had a migration background. Only about 18% reported that the current pregnancy was unwanted. The CG did not receive any study-related interventions but had access to the regular services of the German healthcare system (*treatment as usual*, TAU). This includes the statutory right to midwifery care during pregnancy, childbirth, and the postpartum period, as enshrined in the German Midwifery Act (HebG) and the Midwifery Training and Examination Regulation (HebAPrV).

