**Figure 1 F1:**
[figure not shown]
Flowchart of response rates broken down by IG and CG, with subdivision of IG into CM and TM (t0–t5). IG, intervention group; CG, control group; TM, tandem model; CM, continuous model.

In the CM, *n* = 161 interviews (72.5%) were completed at six months, *n* = 143 (64.4%) at 12 months, *n* = 111 (50.0%) at 24 months, and *n* = 154 (69.4%) at the 7yrs-fu. In the TM, *n* = 104 interviews (60.5%) were completed at six months, 84 (48.8%) at 12 months, *n* = 67 (39.0%) at 24 months, and *n* = 120 (69.8%) at the 7yrs-fu. These figures refer solely to completed interviews and do not reflect program participation.

Sandner and Jungmann (57), based on the BSID-II, found lower rates of cognitive developmental delay among girls in the intervention group compared to the control group, even after adjustment for relevant risk factors. This advantage was evident in the first year of life and persisted in attenuated form into the second year, whereas no differences were observed for boys. A dimensional analysis of the BSID-II further indicated consistently small, though not consistently significant, effects for girls. Sierau et al. (54), and Sandner et al. (68) identified small but statistically significant differences in favor of the intervention group with respect to parental self-efficacy, perceived social support, and reduced stress. No effects were observed for parenting behavior, attachment, empathy, locus of control, life satisfaction, children's socio-emotional development, or health-related behaviors. Conti et al. (52), using micro-analytical observations, demonstrated context-dependent improvements in mother–child interactions for mothers and daughters. By contrast, no positive effects, and in some cases even negative effects, were found for boys and their mothers.

Administrative data analyses likewise indicated selective advantages. Sandner et al. (68) reported lower prescription rates of certain medications and higher utilization of dental preventive care during pregnancy, while no consistent differences emerged with regard to children's medical service use. Herrmann et al. (69), in a subsample, found more favorable maternal dental health values in the intervention group. Finally, Sandner (66) documented higher fertility rates and more favorable pregnancy outcomes among mothers in the intervention group.

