Kliem and Sandner (41), in the context of the 7yrs-fu of the German Pro Kind program and based on the preregistered primary outcome domains [see (40)], demonstrated that the intervention produced significant improvements across several key outcome areas. Children in the IG showed lower rates of internalizing, externalizing, and overall behavioral problems compared to the CG, with effects being particularly pronounced among boys. Mothers in the IG also reported higher life satisfaction and reduced psychological distress. In terms of parenting practices, there was a significant reduction in abusive behavior (with boys additionally experiencing fewer instances of neglect) as well as less dysfunctional parenting behavior.

In a differentiated analysis, the effectiveness of the two implementation models of the ProKind program was examined independently. Schepan et al. (42) demonstrated that the CM proved superior in several outcome domains. It showed greater improvements in maternal mental health, maternal life satisfaction, and reductions in both dysfunctional and abusive parenting practices. In addition, the CM displayed tendencies toward advantages in reducing externalizing behavioral problems in children. By contrast, the TM was only effective in reducing children's internalizing behavioral problems. No effects were found for children's academic performance or life satisfaction. Additional analyses by Conti, Kliem & Sandner (70) indicated that only the CM was associated with a significant reduction in the 12-month prevalence of affective disorders (ICD F30–F39) among mothers and hyperkinetic disorders (ICD F90–F98) among children. Moreover, the CM was linked to lower rates of severe accidents requiring hospitalization as well as a tendency toward fewer foster care placements (71).

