## Data analysis

The primary and secondary analyses will be conducted on an intention-to-treat basis. We will standardize and recode all continuous outcomes such that positive values correspond to beneficial effects. The reported effect sizes (ESs) will be interpreted as group differences in standard deviations (SDs) of the CG. Confidence intervals (CIs) for the ESs will be obtained using bootstrap methods with 5,000 replications. One-sided tests (*p* < .05) will be conducted under the assumption that the intervention is not harmful.

Following the analytic strategy used in the 7yrs-fu of ProKind (41), as well as in recent evaluations of the trial (42, 71), to address missing observations from families who did not participate in the follow-up and to account for the imbalance in a few baseline risk factors (e.g., maternal aggression and mental health problems) between IG and CG, treatment effects will be estimated using augmented inverse probability weighting (AIPW) in combination with the “least absolute shrinkage and selection operator” (lasso) to select relevant control and weighting variables (107).

The AIPW technique assigns weights to observed cases based on the inverse of their probability of loss to follow-up estimated by logit functions, thereby mitigating potential selection bias caused by attrition. In a second step a linear weighted function with additional control variables is estimated. The variables used in the logit functions for the weighting and the control variables for the linear weighted function are selected by lasso, a machine learning algorithm. By weighting participants according to their inverse probability of remaining in the study, the analytic sample is reweighted to more closely resemble the original randomized population, thereby improving both internal validity and generalizability of the findings. Due to findings of the last program phase, all primary and secondary outcomes will be analyzed regarding any differential effects, while controlling for children's gender (41) and delivery model (42).

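### Delivery-model contrasts (CM, TM) are planned for every outcome, but the randomisation described protects only intervention versus control, and nothing in the plan ties these contrasts to municipality

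*Protocol article*

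**What the plan says.** Sample at baseline and randomizations procedure describes a single randomisation. Women were "randomly assigned to an intervention group (IG, *n* = 394) or a control group (CG, *n* = 361"), by a biased-coin design "stratified by municipality (urban vs. rural), age (≤18 vs. >18 years), and maternal nationality (German vs. non-German"). Delivery model is neither an arm nor a stratum, and municipality enters only as urban or rural, not as the individual site.

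Adaptation then states that "the ProKind study evaluated two different delivery models for home visits" and argues that the tandem handover might carry structural disadvantages. Neither Adaptation nor Intervention says how a family came to one model or the other. The trial ran in three federal states (Bremen, Lower Saxony and Saxony), which the article describes as socio-economically different.

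The Figure 1 legend describes response rates "with subdivision of IG into CM and TM"; the control group is left whole. Results of completed follow-up phases reports earlier effects separately by model and says that a previous analysis "demonstrated that the CM proved superior in several outcome domains".

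Data analysis plans that "all primary and secondary outcomes will be analyzed regarding any differential effects", naming child gender and delivery model. It says that it follows the strategy of the earlier evaluations, including the model-specific one. The method is augmented inverse probability weighting (AIPW) with lasso-selected weighting and control variables. Its stated purposes are non-participation at follow-up and baseline imbalance between intervention and control. The comparator for CM or TM is not named.

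**The concern.** Randomisation makes intervention and control comparable. As described, it does nothing for CM versus TM, or for one model versus the control group as a whole. If the two models served different places or different kinds of family, those differences would enter the model contrast and be read as an effect of who made the visits.

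The planned adjustment does not settle this. It is not directed at selection into CM or TM. Lasso may drop municipality, and differences that were not measured remain in any case. The Limitations section does not mention the issue. A CM-over-TM result at 15 years could therefore be read as randomised evidence when the article gives no basis for that. This holds however the model term is coded.

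**Working it through.** **1. The plan's own figure.** Inputs from Procedure and re-engagement strategy: one-sided alpha 0.05, power 0.80, allocation 394:361. Formula: detectable effect = (1.645 + 0.842) × √(1/n₁ + 1/n₂).
- N = 700 (365/335): 0.188; stated 0.19.
- N = 530 (277/253): 0.216; stated 0.22.
- N = 450 (235/215): 0.235; stated 0.23.

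These reproduce to within rounding (the third is rounded down slightly). They concern intervention versus control only.

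**2. Size of the models.** From the six-month interview counts: CM 161/0.725 = 222 and TM 104/0.605 = 172; 222 + 172 = 394. The later visits give the same sizes.

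**3. Detectable effects for model contrasts**, same formula, 7-year numbers (CM 154, TM 120, control 258):
- CM versus all controls: 0.253.
- TM versus all controls: 0.275.
- CM versus TM: 0.303.

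**4. Possible bias.** Assumptions: model followed location; controls split across locations 222:172; no adjustment; outcomes k SD better in CM places than in TM places, whatever the treatment. With f = 222/394 = 0.563:
- CM versus all controls: (1 − f)k = +0.44k.
- TM versus all controls: −fk = −0.56k.
- CM minus TM: k.

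| k (SD) | CM vs all controls | TM vs all controls | CM − TM | One-sided false-positive rate, CM vs all controls (154 vs 258) |
|---|---|---|---|---|
| 0.1 | +0.04 | −0.06 | 0.1 | 11% |
| 0.2 | +0.09 | −0.11 | 0.2 | 22% |
| 0.3 | +0.13 | −0.17 | 0.3 | 36% |

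The nominal rate is 5%. The documents give no value for k. If model was randomised within site, the bias is zero.

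**5. Is there evidence of a different family mix?** Completed interviews, CM versus TM:
- 6 months: 161/222 versus 104/172 (72.5% vs 60.5%), p = 0.011.
- 12 months: 143/222 versus 84/172 (64.4% vs 48.8%), p = 0.002.
- 24 months: 111/222 versus 67/172 (50.0% vs 39.0%), p = 0.029.
- 7 years: 154/222 versus 120/172 (69.4% vs 69.8%), p = 0.93.

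These differences arose after families entered the models, so they show different early attrition. They do not show different families at the start.

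**6. Precision under same-municipality controls.** SE = √(1/n₁ + 1/n₀) in SD units, 70% response: CM 155.4, TM 120.4, control 252.7, the last split 142.4/110.3 under the 222:172 assumption.
- CM: √(1/155.4 + 1/252.7) = 0.102, rising to √(1/155.4 + 1/142.4) = 0.116.
- TM: √(1/120.4 + 1/252.7) = 0.111, rising to √(1/120.4 + 1/110.3) = 0.132.
- CM minus TM: √(1/155.4 + 1/120.4) = 0.121 directly, against √(0.116² + 0.132²) = 0.176 as a difference of two within-municipality effects with separate controls.

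**The case against.** A reader might infer that CM and TM were allocated by site and that each is to be compared with the undivided control group, so that the earlier CM advantage is a site effect. The documents do not support that.
- On allocation the article is silent. It does not say site, choice or a second randomisation. It is a condensed account of a follow-up, and papers on the original trial that are not shown may give the mechanism.
- The whole-control comparator is an inference from an undivided control group in a response flowchart and from earlier model-by-model results. A CM versus TM contrast within the intervention group fits the wording of Data analysis equally well.
- AIPW with lasso may reduce measured imbalance, so the unadjusted bias figures are illustrations and not estimates.
- The early completion gap could itself be a consequence of the tandem handover, and it is gone at 7 years.
- All ten hypotheses in Table 1 concern the home visits as a whole. Data analysis makes no superiority claim; that phrase summarises an earlier paper.

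All of this stands, and it limits the point to confounding that is not excluded. It does not remove the point. The model analyses are planned for every primary and secondary outcome, only the intervention/control comparison is shown to be randomised, and the stated adjustment neither targets the model contrast nor guarantees that municipality is kept.

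**Conclusion.** The concern holds in a limited form. As described, randomisation protects intervention versus control. The protocol does not show that it protects any contrast involving delivery model, and the planned adjustment does not close that gap. Confounding by location or family mix is possible but not demonstrated.

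Its size is unknown. Under the assumptions in the working, a location difference of 0.1 to 0.3 SD passes in full into CM minus TM, where about 0.30 SD is detectable at the 7-year numbers. Against all controls, about 0.44 of it enters the CM effect and 0.56, with opposite sign, the TM effect. With random allocation within site it is zero. The change is worth making because it protects against location bias however CM and TM were assigned, and it uses data already held. The main intention-to-treat result is not in question.

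**What to change.** In Data analysis:
1. State how families came to CM or TM, and name the control set for each model contrast.
2. Force municipality or site into the delivery-model contrasts instead of leaving it to lasso.
3. Estimate each model's effect against control women from the municipalities where that model was delivered.
4. Report CM minus TM as the difference of these within-municipality effects.
5. Label the model contrasts non-randomised and exploratory, with no superiority claim, unless a random CM/TM allocation is documented. The label is needed even with steps 2 to 4: a difference between places in how well any programme works, or selection of families into models within a place, would remain.

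Cost: wording and a filter on the control group, plus precision. With controls split 222:172 and 70% response, the standard error goes from about 0.102 to 0.116 SD for CM and from 0.111 to 0.132 SD for TM. For CM minus TM it goes from 0.121 to about 0.176 SD if the two models share no municipalities. The overall intervention versus control analysis is unchanged.

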## Intervention

After enrollment in the project, participants were usually visited at home every two weeks, either exclusively by specially trained family midwives (CM) or sequentially by a tandem team of family midwives and social workers (TM). Exceptions included a weekly visit schedule in the first month of the intervention and during the 8th–12th weeks of the child's life, as well as a monthly visit schedule in the last three months of the intervention before the child's second birthday. Each home visit followed a structured procedure. In accordance with the NFP program six focus areas (domains) are addressed while working with the participants in the intervention setting. These domains are generally regarded as the most important risk and protective factors for the prevention of negative pregnancy outcomes, child abuse or neglect, developmental delay and limited economic independence. The topics of each visit were divided into six domains:
1.Maternal Health: This area was the focus during pregnancy and covered topics such as managing physical changes, birth preparation, healthy nutrition, physical activity, sleep, oral hygiene, and the consumption of nicotine, alcohol, and substances.2.A Healthy Environment: This involved an assessment of the home environment, the implementation of safety measures to prevent accidents, securing household items, and addressing issues such as mold and secondhand smoke.3.Personal Future Plans: The focus was on future planning (including returning to education or work, and further family planning), as well as organizing daily life and identifying personal strengths and weaknesses.4.Maternal/Parental Role: This area took up most of the time during home visits from the birth of the child until the child's second birthday. It covered topics such as infant care, nutrition, development, parenting, and promoting positive parent-child interactions.5.Social Networks: This addressed social support from partners, parents, and friends, the maintenance of family and friendship relationships, conflict resolution, and non-violent communication.6.Use of Social and Health Services: Information was provided about services important for addressing immediate needs and building support networks, including prenatal check-ups, child health examinations, mother-child groups, and official appointments.A total of *K* = 62 home visitors delivered the intervention, consisting of *k* = 37 midwives, *k* = 24 social workers, and one pediatric nurse. The average age of the home visitors was 40 years (*SD* = 7.8) at the start of the intervention. All home visitors were female and held German nationality. Each home visitor underwent approximately 16 days of in-service training, following the NFP curriculum. The NFP guidelines were translated into German, supplemented with culturally and contextually appropriate materials, and delivered by the German supervisory team. Training sessions covered program theories and their practical applications, including guidelines and specific intervention modules. While there were some profession-specific training modules (e.g., client-centered communication for midwives, feeding practices in early childhood for social workers), the curriculum was generally consistent across both staffing models. Moreover, home visitors received about one hour of clinical supervision weekly. All supervisors (*N* = 6, each with a degree in social work or psychology and additional coaching qualifications) completed a five-day training on the core principles of the program at the NFP National Office in the United States. Overall, the families received an average of 32.7 visits (*SD* = 18.6), with a range of 0–94 visits, which is slightly comparable with U.S. NFP trials ranging from approx. 28 visits (Denver) to approx. 33 visits (Memphis) [see (66)]. Furthermore Sandner (66) demonstrates that the typical distribution of visit content across pregnancy, infancy, and toddlerhood in ProKind closely matched NFP averages and recommendations, particularly in core areas such as maternal health, maternal and parental role, and life course development. Across all families, approx. 13.000 home visits were conducted within the Pro Kind project. The average length of a home visit was 82 min (*SD* = 12.4). Families in the CM received on average 32.4 visits (*SD* = 18.1), while those in the TM received 33.0 visits (*SD* = 19.4), with no statistically significant difference between the two groups. The average duration of the visits was 82.6 min (*SD* = 12.4) in the CM and 79.6 min (*SD* = 14.3) in the TM.

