Consistent with the second phase of the ProKind study, information is collected regarding prior employment, periods of unemployment, welfare receipt, participation in qualification programs during unemployment, and employment details from the Technical Data Center (FDZ) of the IAB in Nuremberg, which is part of the German Federal Employment Agency. Participants had the option to provide self-reported data but withhold permission for researchers to access administrative data. Furthermore, the data linkage with the EMA allows access to official records on mortality of both children and mothers as well as on further births of the participating mothers and their children. Regular inquiries are made to the Federal Central Criminal Register (Bundeszentralregister, BZR). This register records criminal convictions by German courts, certain decisions by administrative authorities, notes on incapacity to be held criminally responsible, and special judicial determinations, as well as subsequent decisions and facts related to these entries. When the relevant conditions are met, foreign convictions of German nationals or individuals born or residing in Germany are also entered into the register. An anonymized report for scientific research purposes is unrestrictedly possible.

Power analyses indicated that with a one-sided test at *α* = .05 and statistical power of 1–*β* = .80, the trial is adequately powered to detect small effects. Calculations were based on the original allocation proportions of the study (*n* = 394 in the IG and *n* = 361 in the CG). Three scenarios were considered. Scenario 1 assumes administrative data with an expected re-engagement of 93% (*n* ≈ 700) which allows the detection of effects of at least ES = 0.19. Scenario 2 assumes a response rate of about 70% (*n* ≈ 530) as observed in the 7yrs-fu (41) which allows the detection of effects of at least ES = 0.22. Scenario 3 assumes a more conservative retention rate of 60% (*n* ≈ 450) which allows the detection of effects of at least ES = 0.23. According to Cohen (93), these values correspond to small effect sizes.

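### Neither the power figures nor the planned inference allows for intervention families sharing home visitors; this matters little for IG versus CG but could matter for the delivery-model contrasts

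*Protocol article*

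**What the plan says.** Under Intervention, the article reports that "62 home visitors delivered the intervention, consisting of" 37 midwives, "24 social workers, and one pediatric nurse". Under the section on the baseline sample and randomization, the control group receives usual care with no study intervention, so only the intervention arm has visitors.

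Under Adaptation, CM families were visited by midwives only. In the TM, "the midwife conducted visits during pregnancy, while the social worker took over approximately two months after the birth". The same section states that "the quality of the relationship between practitioner and family is a key driver of effectiveness in preventive home-visiting programs" and uses continuity with one professional as the reason to expect the CM to do better.

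The power statement, under Procedure and re-engagement strategy, uses a "one-sided test at *α* = .05 and statistical power of 1–*β* = .80". It adds: "Calculations were based on the original allocation proportions of the study". It names no ICC and no design effect.

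Under Data analysis, effects are estimated by AIPW with lasso selection, and "Confidence intervals (CIs) for the ESs will be obtained using bootstrap methods with 5,000 replications". The resampling unit is not named. Differential effects by child gender and delivery model are planned for all primary and secondary outcomes.

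**The concern.** This is a partially nested design: intervention families share a limited number of visitors and control families share none. If the visitor matters for outcome, as the article argues, the intervention-arm mean carries a between-visitor variance component that resampling single families does not capture. Intervals would then be too short and one-sided tests would reject somewhat more often than 5% under the null.

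The pooled comparison is partly protected because one arm is unclustered and caseloads per visitor are moderate. The delivery-model analyses are less protected. Each model has fewer visitors, and in a direct CM versus TM contrast both sides are clustered. The 7-year results drew separate conclusions for the two models, so these analyses carry weight.

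**Working it through.** **Inputs from the article.** One-sided α = .05, power .80, allocation 394:361; scenarios of about 700, 530 and 450 families with detectable effects 0.19, 0.22 and 0.23. Visitors: 62, of whom 37 are midwives and 24 social workers. Interviews at the 7-year follow-up: CM 154, TM 120, CG 258.

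**Assumptions.** Visitor ICC .01 to .05 (none is given), equal caseloads, and no gain from covariate adjustment. The number of intervention clusters is taken as 62 (every visitor a separate cluster) or 37 (midwives only). Because TM families had two visitors in sequence, neither count is exact.

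**Step 1: reproduce the published power.** MDE = (1.645 + 0.842) × √(1/n_IG + 1/n_CG).

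- n = 700 (365/335): 0.188
- n = 530 (277/253): 0.216
- n = 450 (235/215): 0.235

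These agree with 0.19, 0.22 and 0.23 to rounding (power at the stated effects 0.81, 0.81 and 0.79). The figures therefore assume independent families, with no allowance for clustering.

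**Step 2: cluster the intervention arm, Scenario 2.** DE = 1 + (m − 1) × ICC, with m the families per visitor; SE = √(DE/n_IG + 1/n_CG). With 62 clusters m ≈ 4.5; with 37, m ≈ 7.5.

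| Clusters | ICC | DE | SE change | MDE |
|---|---|---|---|---|
| 62 | .01 | 1.035 | +0.8% | 0.218 |
| 62 | .02 | 1.069 | +1.6% | 0.220 |
| 62 | .05 | 1.173 | +4.1% | 0.225 |
| 37 | .01 | 1.065 | +1.5% | 0.220 |
| 37 | .02 | 1.130 | +3.0% | 0.223 |
| 37 | .05 | 1.324 | +7.5% | 0.232 |

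At ICC .05, power for an effect of 0.22 falls from 0.81 to 0.78 (62 clusters) or 0.76 (37). The actual one-sided error of a nominal 5% test, 1 − Φ(1.645/SE ratio), is 5.7% or 6.3%.

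**Step 3: CM versus TM at the 7-year numbers (154 and 120).** Ignoring clustering, MDE = 2.487 × √(1/154 + 1/120) = 0.303. TM clusters are taken as the 24 social workers. CM clusters run from 37 (every midwife worked in the CM) to 13 (37 − 24, if each social worker had her own midwife partner outside the CM).

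| CM clusters | ICC | DE in CM / TM | SE change | MDE |
|---|---|---|---|---|
| 37 | .01 | 1.032 / 1.040 | +1.8% | 0.308 |
| 13 | .01 | 1.108 / 1.040 | +3.4% | 0.313 |
| 37 | .05 | 1.158 / 1.200 | +8.7% | 0.329 |
| 13 | .05 | 1.542 / 1.200 | +16.2% | 0.352 |

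At ICC .05 the one-sided error would be 6.5% to 7.8%.

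**Step 4: each model against CG (258), ICC .05.** CM versus CG: SE +4.8% (37 clusters) to +15.7% (13). TM versus CG: +6.6%.

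**The case against.** A reader might infer that the plan resamples single families and that its intervals are therefore wrong. The article does not say so: it gives the method and the number of replications and is silent on the unit. An article may leave that detail to a full analysis plan, which could specify a cluster bootstrap. Independence is demonstrated for the power figures only.

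A reader might also take too-short intervals as established. They require a positive ICC in outcomes about 15 years on, and none is documented. General evidence that the relationship drives effectiveness does not show that families sharing a visitor have correlated outcomes in adolescence. Exposure ranged from 0 to 94 visits, and 166 of 394 mothers left early, 52 of them before birth, which may dilute any correlation. Near an ICC of zero nothing changes.

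The pooled effect is small: at ICC .05 the detectable effect rises to about 0.23, a value the article already quotes for Scenario 3, so the claim of power for small effects stands.

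The largest figures depend on a visitor count per model that is not reported, and on a head-to-head CM versus TM test that is not explicitly specified. Simple nesting in 62 visitors is also too strong a description, since TM families changed visitor.

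All of this stands, and it makes the point conditional. It does not remove it: the published power has no allowance for visitors, the analysis description mentions none, and the contrasts of each model with CG are affected as well.

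**Conclusion.** The point holds in conditional form. The power figures assume independent families, and the described inference makes no allowance for shared visitors, although the article treats the visitor relationship as a mechanism of effect. If families are resampled singly and the visitor ICC lies in the assumed .01–.05, the standard error is understated by about 1–7% for IG versus CG. For CM versus TM it is about 2–3% at ICC .01 and 9–16% at .05. Unequal caseloads would raise these figures; covariate adjustment could offset part of them.

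The documents do not support saying that the planned intervals are wrong or that the trial is underpowered for its main comparison. This is an inexpensive improvement in method that matters mainly for the delivery-model analyses.

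**What to change.** State the resampling unit. In the bootstrap, resample intervention families in blocks defined by the first assigned visitor, and control families singly. The first visitor is normally the midwife, who is defined also for TM mothers who left before the handover; blocking TM families by social worker alone would leave those mothers without a block, although the intention-to-treat analysis needs them. Families never assigned a visitor form single-family blocks. As a check, repeat the analysis with TM families blocked by social worker where there was one.

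Apply this at least to the delivery-model analyses, and report the number of visitors and caseloads per model. Quote the detectable effects over a stated ICC range, for example .01 to .05, alongside the current figures.

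The cost is a visitor identifier in the analysis file and a changed resampling step; no new participant data are needed. Where the ICC is positive, intervals become wider, by a few per cent for the pooled contrast and possibly by more than 10% for CM versus TM.
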